### Measures

#### Overview of Measures

Feasibility is the primary outcome for the study, and the secondary outcomes relate to relationship communication, ART adherence, and changes in HIV viral load. Feasibility will be assessed for intervention participants, whereas the secondary outcomes will be assessed for both study arms. Survey measures, interviews, and a biomedical marker of viral load will be used.

#### Feasibility Surveys

There are 4 domains of feasibility—feasibility [49], acceptability [50], willingness [24], and safety [51]. Feasibility is the ability to recruit participants, retain participants, send and receive messages, and participate in group sessions [49]. Acceptability is the degree to which participants like or dislike components of the intervention [52]. Willingness refers to participants’ interest in enrolling in a longer trial and recommending the intervention to others [24]. Safety is the ability to ensure the confidentiality and security of participant data and communication within and outside the intervention [51]. To assess acceptability, the Self-Intervention Evaluation Form and the Client Satisfaction Questionnaire will be administered [53,54]. In addition, a study-specific Likert scale survey will be developed to assess feasibility, willingness, and safety [34]. The study-specific survey will assess participants’ perceived ability to send and receive messages and participate in group sessions and group check-ins (feasibility), the likelihood of participants enrolling in a longer study or referring other GBMSM (willingness), the likelihood of participants providing partners a referral letter (willingness), and perceived intervention confidentiality and security (safety).

#### Feasibility Interviews

In order to understand the feasibility domains, we will conduct 30-minute interviews with purposively selected intervention arm participants (n=30) based on their intervention engagement at baseline, midintervention, and postintervention [55]. Feasibility will be measured by examining participants’ attitudes toward various aspects of the intervention, including video-group interactions; referral letters; and perceived changes in the ability to self-manage ART, HIV risk, and HIV disclosure [56]. Acceptability will be evaluated by examining whether participants like or dislike intervention components and the intervention as a whole [56]. Willingness will be assessed by measuring participants’ willingness to use the intervention from beginning to end, their willingness to use the intervention in different contexts, and their willingness to suggest the intervention to others [56]. Safety will be examined by measuring participants’ perceived levels of discomfort with different components of the intervention and their perceptions of personal safety and unwanted disclosures [51].

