#### Relationship, ART Adherence, and Biomedical Measures

Although our study is not powered to detect changes in these areas, the outcomes from these measures will identify potential directions of effect and inform power calculations for a future efficacy trial. Central to the intervention is creating skills for GBMSM living with HIV to talk to their partners about HIV. The key area—relationship satisfaction—will be assessed by using a 10-item scale that assesses satisfaction with both the partner and the relationship [57]. Communication with partners will be assessed by using the short form (11 items) of the Communications Patterns Questionnaire, which assesses communication and conflict resolution [58]. Disclosure will be measured by using both Kalichman and Nachimson’s [59] HIV Disclosure Intent Scale and study-specific questions asking whether the participants disclosed their HIV status to their partners. The questions will also explore participants’ partners’ reactions, the participant-reported partner uptake of a referral letter, and the reported uptake of HIV testing by a partner. HIV treatment adherence will be assessed by using a visual analog scale [60], and HIV viral load testing will be conducted by using dried blood spots. Relationship and ART adherence measures will be administered from baseline through follow-up, and biomedical measures will be administered at baseline and postintervention to all randomized participants.

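### Personal safety and unwanted disclosure are named only as interview topics for 30 of the 60 SOAR participants; no structured item on either is described for all randomized men.

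*Protocol article*

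**What the plan says.** All references are to the protocol article.

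- **Overview of Measures** names feasibility as the primary outcome and limits it to one arm: "Feasibility will be assessed for intervention participants, whereas the secondary outcomes will be assessed for both study arms".
- **Feasibility Surveys** lists safety as one of four feasibility domains and defines it narrowly: "Safety is the ability to ensure the confidentiality and security of participant data and communication within and outside the intervention". The study-specific survey, still to be developed, covers "perceived intervention confidentiality and security (safety").
- **Feasibility Interviews** takes a wider view of safety. It includes discomfort with intervention components and "their perceptions of personal safety and unwanted disclosures". The interviewees are "purposively selected intervention arm participants (n=30) based on their intervention engagement".
- **Relationship, ART Adherence, and Biomedical Measures** includes "study-specific questions asking whether the participants disclosed their HIV status to their partners", and adds: "The questions will also explore participants’ partners’ reactions". It also lists scales for relationship satisfaction and for communication and conflict resolution. These run from baseline through follow-up, and under Overview of Measures the secondary outcomes cover both arms.
- **Attention-Matched Control Procedures** has controls receive video links by text message weekly for 5 weeks and one-way text messages weekly for 3 months. The control topics include sexuality.

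**The concern.** The safety content closest to actual personal harm has the narrowest stated coverage. A man can rate the video sessions as confidential and still have been exposed or threatened at home; the survey as described would not record that.

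The point matters in this population. Under Aim 2 Participants, every man enrolled has not told his partner his HIV status, and the partner is HIV negative or of unknown status. The Background section reports that men skip or stop ART to avoid being exposed involuntarily, and that partner rejection keeps men from treatment. Both arms get study messages on their phones, so involuntary disclosure can arise in either arm, and a one-arm account has no background rate. Unrecorded events could also blur the adherence and viral load signals that the pilot is meant to pass on to the next trial.

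**Working it through.** **The plan's own figure.** Statistical Analysis states 70% power with 46 per group for 30% v 55% at a type 1 error rate of .05 (taken as two-sided).

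- Pooled standard error under no difference: √(2 × 0.425 × 0.575 / 46) = 0.1031.
- Standard error under the alternative: √((0.30 × 0.70 + 0.55 × 0.45) / 46) = 0.0997.
- Power = Φ((0.25 − 1.96 × 0.1031) / 0.0997) = 68.5%. Using the unpooled standard error throughout gives 70.8%.
- Retention: 120 × 0.77 = 92.4, so 92, or 46 per group.

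Both stated figures reproduce, and this point changes neither. They supply the arm size (60) and the expected number retained (46).

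**Chance of seeing no case.** With n people asked and true rate p, this is (1 − p)^n. The documents give no harm rate, so p is an assumption shown over a range.

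| Assumed rate | n = 30 (interviews) | n = 46 (retained) | n = 60 (whole arm) |
|---|---|---|---|
| 1% | 74% | 63% | 55% |
| 2% | 54% | 40% | 30% |
| 5% | 21% | 9.4% | 4.6% |
| 10% | 4% | 0.8% | 0.2% |

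**Upper bound after zero events.** The one-sided 95% limit is 1 − 0.05^(1/n) and needs no assumed rate: 9.5% for n = 30, 6.3% for n = 46, 4.9% for n = 60.

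**Finite-arm view.** If k of the 60 SOAR participants had such an event, a random 30 would include none of them with probability C(60 − k, 30) / C(60, 30): 50% for k = 1, 25% for k = 2, 12% for k = 3.

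All three calculations treat those asked as a random sample. The 30 are chosen purposively, so the results for them are only a guide.

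**What asking controls would add.** For an assumed 5% v 15%, two-sided at .05, pooled:

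- 46 per arm: Φ((0.10 − 1.96 × √(2 × 0.10 × 0.90 / 46)) / √((0.0475 + 0.1275) / 46)) = Φ(−0.37) = 36%.
- 60 per arm: the same formula gives Φ(−0.14) = 45%.

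A between-arm contrast would therefore be descriptive. The gain is mainly in detection.

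**The case against.** Much can be said for the plan.

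1. A reader might infer that harms of disclosure cannot be compared between arms at all. The article does not support that. Disclosure, partner reactions, relationship satisfaction and conflict resolution are secondary outcomes measured in both arms, so rejection or conflict after disclosure can be compared. Nor does the text confine the partner-reaction questions to men who chose to disclose. This stands and narrows the point.
2. An overheard session or an intercepted message is a breach of confidentiality, and the survey asks about perceived confidentiality beyond the 30 interviewees. This stands in part: it covers one route to exposure in the SOAR arm, but not personal safety, and nothing in controls.
3. A reader might infer that selecting on engagement leaves out men who were harmed and withdrew. The article does not say whether high or low engagers are sought; purposive selection could deliberately include the latter. The direction of any bias is unknown.
4. Group sessions and referral letters belong to the SOAR arm, so controls give no background rate for those routes. This stands, but messages and links go to both arms.
5. This is a condensed article, and reporting of adverse events or social harms may sit in the full protocol. Its absence here does not show that it is absent. Such reporting would not alter what the article does state: this domain of the primary outcome is assessed in one arm, and its personal-harm content in a subset.
6. The pilot plans no comparative conclusion on safety. True; the point concerns detection and description.

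**Conclusion.** The narrow point holds. Safety is a domain of the primary outcome, yet it is assessed in SOAR participants only, and personal safety and unwanted disclosure are named only for 30 of those 60. No structured item on either is described for all randomized men.

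At an assumed 5% rate, a harm would go unseen with probability 21% when 30 are asked, against 9.4% with 46 and 4.6% with 60. The bound after zero events is about twice as wide with 30 as with 60. These sizes rest on assumed rates and on random sampling, which purposive selection does not provide. The stronger readings, that no harm can be compared or that harmed men will be under-sampled, are not supported by the article. The gap is worth closing while the survey is being developed; it does not undermine the pilot's design.

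**What to change.** Add a few fixed items to the relationship questionnaire that both arms already complete from baseline through the 28-week follow-up: unwanted disclosure of HIV status (to the partner or anyone else), threats or violence, and loss of the relationship. Report counts by arm among all randomized participants, state how many answered, and present the comparison as descriptive. Keep the 30 interviews to explain context.

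The cost is a handful of items for 120 people and slight added burden for respondents. No extra visits or staff are needed.

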#### Relationship, ART Adherence, and Biomedical Measures

Although our study is not powered to detect changes in these areas, the outcomes from these measures will identify potential directions of effect and inform power calculations for a future efficacy trial. Central to the intervention is creating skills for GBMSM living with HIV to talk to their partners about HIV. The key area—relationship satisfaction—will be assessed by using a 10-item scale that assesses satisfaction with both the partner and the relationship [57]. Communication with partners will be assessed by using the short form (11 items) of the Communications Patterns Questionnaire, which assesses communication and conflict resolution [58]. Disclosure will be measured by using both Kalichman and Nachimson’s [59] HIV Disclosure Intent Scale and study-specific questions asking whether the participants disclosed their HIV status to their partners. The questions will also explore participants’ partners’ reactions, the participant-reported partner uptake of a referral letter, and the reported uptake of HIV testing by a partner. HIV treatment adherence will be assessed by using a visual analog scale [60], and HIV viral load testing will be conducted by using dried blood spots. Relationship and ART adherence measures will be administered from baseline through follow-up, and biomedical measures will be administered at baseline and postintervention to all randomized participants.

### Statistical Analysis

Based on our experience from prior studies, we expect around a 23% loss to follow-up, which will result in 92 participants; therefore, we expect to retain 46 participants per group from enrollment through follow-up at 28 weeks. Like other pilot studies, ours is not powered to show the efficacy of the intervention in the study population; the aim of the study is to establish feasibility and the preliminary impact on HIV treatment outcomes before moving to a larger efficacy trial powered for clinical outcomes. We will be able to assess the preliminary impact of SOAR on ART adherence, behavioral measures, and viral load measures. To this end, our sample size (46 participants per group in the randomized controlled trial, yielding data on 92 participants) will yield 70% statistical power with a type 1 error rate at .05 to show a difference between a behavior frequency of 30% in the attention-matched control group and a behavior frequency of 55% in the intervention group for all outcomes.

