#### Usability

The intervention will be pretested for usability over a 5-week period in 2-hour sessions (1 session per week). A group check-in will then be conducted 3 weeks after participants’ last session (week 8). A group of participants (n=7) will complete all 5 sessions together on Zoom (Zoom Video Communications Inc). During the last session, participants will be informed of the date and time for the group check-in session. During the pretest, the interventionist will monitor participants’ engagement and follow up with participants who miss a session. Before beginning the pretest, each participant will provide their mobile number to receive group session reminders. All intervention sessions and group check-ins will be video recorded for analysis. All participants will receive a data plan to complete this task.

After the pretest, interviews will be conducted with GBMSM participants, and a focus group will be conducted with health care and IT experts. The interviews with GBMSM participants will cover the following six intervention usability domains [47]: (1) the functionality of sessions with group check-ins, (2) the timeliness and appropriateness of sessions, (3) the clarity of session content delivery, (4) the clarity and management of self-assessments and action plans, (5) incomplete sessions, and (6) the technical transition between sessions and between sessions and group check-ins. The focus group with health experts will involve a presentation of the intervention data that are collected from the pretest. This presentation will include a video recording of 1 session, interview results, and technical challenges. Health experts will be asked to provide their perspective on how these pretest findings will influence the pilot intervention and what corrections are needed to limit the number of incomplete group sessions and technical challenges, in order to improve usability. The findings will be integrated into the final intervention and named *SOAR* for the pilot test in the randomized controlled trial (aim 2).

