### Intervention Arm Procedures

#### Group Sessions

Participants will receive the intervention for 5 weeks in 2-hour sessions (1 session per week). Participants will complete the session with the same group of GBMSM. After providing consent, participants will complete Zoom training, which will include a simulated conversation with the interventionist, who will use Zoom in the same room as the participants. Then, each participant’s smartphone will be assessed and set up for compatibility for Zoom. Participants will be notified that they will receive an SMS text message reminder 12 hours before each session. At 1 hour before a session, participants will receive an SMS text message with the Zoom link for that session. Participants will complete several self-assessments and develop an action plan during the intervention. Participants will be provided with the partner referral letters via SMS text messaging (REDCap [Research Electronic Data Capture]; Vanderbilt University) or in paper form (their choice) at the start of the study; multiple copies of the referral letters may be requested throughout the study.

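### The 70% power figure treats 92 participants as independent, although SOAR is delivered in fixed groups in one arm only; any within-group correlation makes power lower than stated

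*Protocol article*

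**What the plan says.** The Statistical Analysis section of the protocol article bases its figure on "46 participants per group in the randomized controlled trial, yielding data on 92 participants", after allowing for dropout: "we expect around a 23% loss to follow-up, which will result in 92 participants". It then claims that this sample "will yield 70% statistical power with a type 1 error rate at .05 to show a difference between a behavior frequency of 30"% in controls and "a behavior frequency of 55% in the intervention group for all outcomes". It mentions no ICC, design effect, group size or number of groups.

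Aim 2 Participants has individuals randomized 1:1, 60 to each arm. Delivery then differs by arm:

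- **SOAR.** Five weekly 2-hour sessions, of which Group Sessions says: "Participants will complete the session with the same group of GBMSM". Group Check-ins adds three further group meetings by videoconference.
- **Control.** Attention-Matched Control Procedures describes five videos sent as web links and weekly one-way text messages. Participants are not placed in groups.

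The only group size in the article belongs to the aim 1 pretest, under Usability: "A group of participants (n=7) will complete all 5 sessions together on Zoom". None is given for the pilot trial.

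**The concern.** People who share a facilitated group over several months tend to have outcomes more alike than people who do not. Here that is close to the intended mechanism, since the Theoretical Framework section relies on skill building in a confidential group setting. A calculation with zero within-group correlation in the SOAR arm fits poorly with that rationale.

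Two things are at stake. First, the article attaches a specific power to every outcome, and with any positive ICC that power is overstated. Second, the section on relationship, ART adherence and biomedical measures says that these outcomes will inform the power calculation of a later efficacy trial. If the independence assumption is carried forward, the group-delivered arm of that larger trial could be undersized.

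**Working it through.** **Inputs from the article.** 46 analysed per arm (120 × 0.77 = 92.4, so 92 in total); proportions 0.30 and 0.55; type 1 error 0.05. Sidedness is not stated; two-sided reproduces the figure (one-sided gives 79.0%).

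**Inputs assumed.** Group size at enrolment 7 (the pretest size) or 10 (no source in the article). Scaling by 46/60 gives m = 5.37 or 7.67 retained per group. The number of groups is 60/7 ≈ 8.6 or 60/10 = 6. ICC 0.02, 0.05 and 0.10.

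**Step 1: reproduce the stated figure under independence.** The mean proportion is (0.30 + 0.55)/2 = 0.425.

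- Null SE = √(2 × 0.425 × 0.575 / 46) = 0.1031
- Alternative SE = √((0.30 × 0.70 + 0.55 × 0.45) / 46) = √(0.4575/46) = 0.0997
- Pooled: z = (0.25 − 1.96 × 0.1031)/0.0997 = 0.481, power 68.5%
- Unpooled: z = 0.25/0.0997 − 1.96 = 0.547, power 70.8%

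These two values bracket 70%, so nothing is held back for clustering.

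**Step 2: add clustering to the SOAR arm only.** DE = 1 + (m − 1) × ICC.

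- Null SE = √(0.425 × 0.575 × (1 + DE)/46)
- Alternative SE = √((0.21 + DE × 0.2475)/46)

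Example, m = 7.67 and ICC 0.05: DE = 1 + 6.67 × 0.05 = 1.333. Null SE = √(0.2444 × 2.333/46) = 0.1113. Alternative SE = √((0.21 + 0.33)/46) = 0.1083. z = (0.25 − 1.96 × 0.1113)/0.1083 = 0.293, power 61.5%.

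**Step 3: type 1 error if the groups are ignored.** With equal proportions in both arms, the true SE exceeds the assumed one by √((1 + DE)/2), so the error is 2 × (1 − Φ(1.96/√((1 + DE)/2))).

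| m | ICC | DE | Effective n, SOAR (46/DE) | Power, pooled | Power, unpooled | Type 1 error if groups ignored |
|---|---|---|---|---|---|---|
| 5.37 | 0.02 | 1.09 | 42 | 66.5% | 68.8% | 5.5% |
| 5.37 | 0.05 | 1.22 | 38 | 63.8% | 65.9% | 6.3% |
| 5.37 | 0.10 | 1.44 | 32 | 59.6% | 61.6% | 7.6% |
| 7.67 | 0.02 | 1.13 | 41 | 65.6% | 67.8% | 5.8% |
| 7.67 | 0.05 | 1.33 | 34.5 | 61.5% | 63.6% | 7.0% |
| 7.67 | 0.10 | 1.67 | 28 | 55.7% | 57.5% | 9.0% |

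Weighting the pooled proportion by effective sample size moves the pooled column by at most about one point (at ICC 0.10 it becomes 57-60% instead of 56-60%).

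**Step 4: the same thing as precision.** The 95% half-width for the difference is 1.96 × 0.0997 = 19.5 percentage points under independence and 1.96 × 0.1083 = 21.2 points in the example of step 2.

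All of this uses the normal approximation. With about 6 to 9 groups, small-sample degrees of freedom would lower power further.

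**The case against.** The strongest reply is that little depends on this number. Overview of Measures makes feasibility the primary outcome, assessed in the intervention arm, and no between-arm test bears on it. The article disclaims efficacy power in Study Design Overview, in the section on relationship and biomedical measures, and in Statistical Analysis itself. That stands, and it limits the severity. It does not make the printed figure right: having disclaimed efficacy power, the article still asserts a power for all outcomes.

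A second reply is that the size is assumed. That also stands. At ICC 0 nothing changes. At ICC 0.02 the loss is 2 to 3 points, about the gap between the pooled and unpooled formulas and much less than a switch to Fisher's exact test would cost (59.8% under independence). The loss is clearly larger only at ICC 0.05 to 0.10, and the article does not show that such values apply.

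A third reply concerns the analysis. A reader might infer that the trial will have an inflated type 1 error and intervals that are too narrow. The article does not support that: it names no test or model for comparing the arms, and a statistical analysis plan may include a group effect. The 0.05 is an input to a power calculation and does not commit the trial to an unclustered test. A reader might also infer that the pilot cannot yield an ICC; nothing prevents estimating one, since participants stay with the same group. Finally, models with a random effect for 6 to 9 small groups and a binary outcome can be unstable, so the analysis remedy is not entirely free.

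**Conclusion.** The power statement is wrong as written, in a limited sense. It is an independent-observations calculation applied to a partially nested design, and for any positive within-group correlation it overstates power. Under the assumed group sizes, power is about 66-67% at ICC 0.02, 62-64% at 0.05 and 56-60% at 0.10, against 68.5% by the same formula without clustering. The direction is secure for any positive ICC. The size is not, because both the ICC and the pilot group size are assumptions.

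The type 1 error of about 5.5-9%, and intervals that are too narrow, follow only if the between-arm comparison ignores the groups. The point is minor to moderate: it affects a secondary claim and the usefulness of the pilot for sizing the next trial, not its feasibility objective.

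**What to change.** - In Statistical Analysis, state the planned SOAR group size and number of groups. Restate power over a range of ICCs with the design effect in the SOAR arm only, or drop the power claim and give the expected width of the interval for the difference.
- For the secondary between-arm comparisons, specify a method that accounts for SOAR group, with controls as singletons and a small-sample correction. If an analysis plan already does this, a cross-reference is enough. Name a fallback in case the model does not converge or estimates the group variance as zero.
- Report the estimated ICC with its interval, and say that with about 6 to 9 groups it will be imprecise and should not be used as a point value for sizing the later trial.

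The cost is a few lines of text and a somewhat more complex model. The power figure becomes less favourable and intervals slightly wider. No participants are added and delivery of the intervention does not change.
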